### Treatment allocation

To ensure comparability between the intervention and the control group, a stratified random allocation design will be used based on sociodemographic values with a 5:1 allocation ratio to intervention and control group. The randomized intervention group consists of participants and decliners. The decliners will not receive any TBHC. However, they will have the opportunity to opt in to the TBHC via a telephone number printed on the questionnaires. In that case, they will be excluded from the study.

Once the patients are assigned to one of the three groups there will be no blinding of coaches, patients or researchers and their assistants. Nevertheless, the coaches will not know who is responding in the study. The questionnaires are pseudonymized.

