### Study procedures

The eligible insureds will be randomized to the intervention and control group. After randomization, members of the intervention group will receive an invitation to take part in the TBHC and an acquisition call. If they send back the confirmation of participation, they will be included in the study as participants. In case they

will not send back the required confirmation, insureds will be grouped as decliners. The control group will receive no invitation.

After completion of the treatment allocation, envelopes will be sent out to the members of the three groups. The first mailing consists of a cover letter, an explanation of the study, information regarding privacy, an informed consent and the questionnaire itself. Six weeks after the first letter, a reminder will be sent out with the same content. In order to limit expenses, just 50% of the decliners who will be randomly selected will receive an envelope (Figure 1).

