### Power calculation

Calculation of the target sample size was based on the patient reported outcomes collected by questionnaire. In order to achieve a power of at least 95% at a type I error rate of  $\alpha = 5\%$  in a two-sided test accounting for the unbalanced group allocation, a minimum of 1,670 patients are needed to be able to detect a small standardized mean difference in group comparisons (Cohen's  $d$  of 0.2) [28] at  $T_2$  following the intention-to-treat principle. Assuming a response rate between 18% and 40% and drop-out rates between 10% and 82% depending on group and phase, a target sample size of approximately 9,000 patients was identified who should be invited to the questionnaire survey. Assuming that around 65% of the invited patients will decline participation and half of them will be followed up, a total of 12,000 patients were targeted (see Figure 1). Because the primary outcome 'time until hospital readmission' is collected from routine data available for the total sample of 12,000 patients from the KKH statutory health insurance, the primary analysis is sufficiently powered to detect even very small effects with a high probability (low type II error).

[figure not shown]

**Figure 1** Expected participant flow for patient-reported outcomes.

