### Control condition

The control group will receive no coaching (treatment as usual). It is possible that the control group will receive the same written information material as the intervention group through other employees of the insurance.

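### Printing the coaching opt-in number on the outcome questionnaires lets survey sampling decide which decliners are re-offered coaching, and excluding those who accept removes randomised patients from the intervention arm only

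*Protocol*

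**What the plan says.** All references are to the protocol.

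- **Treatment allocation.** The randomised intervention group is made up of participants and decliners, under a "5:1 allocation ratio to intervention and control group". Decliners get no coaching, but "they will have the opportunity to opt in to the TBHC via a telephone number printed on the questionnaires". The next sentence sets the consequence: "In that case, they will be excluded from the study".
- **Study procedures.** After allocation, "envelopes will be sent out to the members of the three groups", with a reminder of the same content six weeks later. To save money, however, "just 50% of the decliners who will be randomly selected will receive an envelope". For controls: "The control group will receive no invitation".
- **Study design.** Measurement is at baseline and at 12, 24 and 36 months.
- **Power calculation.** The assumption is that "around 65% of the invited patients will decline participation and half of them will be followed up, a total of 12,000 patients were targeted", with roughly 9,000 people invited to the survey.
- **Primary outcome and Statistical analysis.** Routine-data outcomes are to cover everyone randomised, about 12,000 insured persons. The primary analysis follows intention to treat with all of them, and Intention-to-treat 1 keeps decliners in the intervention group.

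**The concern.** The questionnaire is the instrument for the patient-reported outcomes, and it also carries a route into the treatment under test. Among decliners, that route goes only to those drawn for the survey. Two consequences follow.

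First, the surveyed half is the only source of patient-reported data on decliners, so in Intention-to-treat 1 it has to stand for all of them. It is followed under a renewed offer of coaching that the other half does not get by this route. The decliners most willing to be coached are then taken out of the surveyed half, while similar people stay in the unsurveyed half.

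Second, the exclusion depends on behaviour after randomisation and, as written, applies only to the intervention arm. If it extends to the routine data, the primary analysis no longer contains everyone randomised. The section that sets the exclusion and the sections that define the analysis population cannot both be followed.

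**Working it through.** **1. Reproduce the plan's survey flow.** Inputs: 12,000 randomised, 65% declining and half of decliners followed up (Power calculation); 5:1 allocation (Treatment allocation).

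- Intervention arm: 12,000 × 5/6 = 10,000. Control arm: 12,000 × 1/6 = 2,000.
- Decliners: 0.65 × 10,000 = 6,500. Participants: 10,000 − 6,500 = 3,500.
- Decliners mailed a questionnaire: 6,500 / 2 = 3,250. Not mailed: 3,250.
- Total mailed: 3,500 + 3,250 + 2,000 = 8,750. This is 2.8% below the stated figure of approximately 9,000, so the flow reproduces.

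**2. Number removed by the opt-in rule.** The protocol gives no opt-in rate q, so I assume 1% to 10% of the mailed decliners. Removed = 3,250 × q; share of the arm = removed / 10,000.

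| Assumed q | Removed | Share of intervention arm |
|---|---|---|
| 1% | 32.5, about 33 | 0.3% |
| 5% | 162.5, about 163 | 1.6% |
| 10% | 325 | 3.3% |

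In the unmailed half, the number removed by this route is zero. The two random halves are therefore treated differently only because one is measured.

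**3. What happens if they are kept.** Coaching uptake in the arm would be (3,500 + 3,250q) / 10,000. That is 35.3% at q = 1% and 38.3% at q = 10%, against 35.0% without opt-ins.

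**4. Illustration of the effect on the primary outcome.** Assumptions, none of them from the protocol: no treatment effect, a two-year readmission risk p of 50% or 75%, and opt-ins with r = 0.8 or 1.2 times the arm's risk. With f the excluded share of the arm:

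- Risk after exclusion: p′ = (p − f·r·p) / (1 − f)
- Apparent hazard ratio: ln(1 − p′) / ln(1 − p)

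Largest case, f = 0.0325 and p = 0.75:

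- r = 0.8: p′ = (0.75 − 0.0195) / 0.9675 = 0.7550; hazard ratio 1.015.
- r = 1.2: p′ = (0.75 − 0.02925) / 0.9675 = 0.7450; hazard ratio 0.986.

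The arm's risk moves by at most about 0.5 percentage points. At q = 1% and p = 0.50 the hazard ratio stays between 0.999 and 1.001.

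**5. Set the rules side by side.** Treatment allocation removes opt-ins from the study. Statistical analysis puts everyone randomised into the primary analysis, and Primary outcome says the routine data cover all of them. No sentence limits the removal to the survey or exempts Intention-to-treat 1 from it.

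**The case against.** The strongest defence is that decliners belong to the arm randomised to be offered coaching. A decliner who later accepts is taking up the assigned offer, which is not contamination between arms, and under Intention-to-treat 1 this would do no harm to the primary comparison if the person were kept. That stands for the routine-data outcome. It does not rescue the plan as written, because the plan removes these people. Nor does keeping them repair the survey: the surveyed half would still have had an offer that came only from being surveyed.

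A second defence is that the half is drawn at random, for reasons of expense, and so represents decliners at baseline. That is true at the draw. Any divergence comes afterwards and depends on an opt-in rate that nobody has stated. How often the offer recurs is also uncertain: the plural "questionnaires" suggests every wave, but the protocol does not say so. The removal might also have been meant for the survey only, which the wording does not say either.

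A reader might go further and infer that controls receive the same form, so that some of them enter coaching, the contrast between arms shrinks and the required sample grows. The documents do not support this. The opt-in sentence concerns decliners, controls are to get neither invitation nor coaching, and no passage says that the control form carries the number or that a calling control would be coached. The mailing to three groups is described without separate versions, but that silence is not evidence of a common form. Late uptake by decliners cannot shrink the contrast either: if they are kept, it raises the coached share in their own arm.

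**Conclusion.** The point holds in a limited form. The outcome questionnaire changes the chance of being coached in a random half of decliners, and the accompanying rule turns that into an exclusion after randomisation in the intervention arm only. This weakens the patient-reported Intention-to-treat 1 analysis, where the surveyed half must represent all decliners, and it contradicts the stated analysis population for the primary outcome.

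The size is modest. The 3,250 mailed decliners follow from the plan's own figures. The number removed, about 33 to 325, rests on an assumed opt-in rate of 1% to 10%. Under the illustrative risks above, the primary hazard ratio would be displaced by no more than about 1.5%. A much higher opt-in rate, or opt-ins whose risk differs more sharply from the arm's, would enlarge this. No contamination of controls and no sample-size inflation should be claimed. The change is worth making because it is inexpensive and removes both the survey-induced exposure and the exclusion at their source.

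**What to change.** 1. Remove the coaching number from every remaining study questionnaire, in all groups and at all remaining waves, and print only a neutral study contact for questions about the survey. This also settles what the control forms carry.
2. Place any opt-in contact in the invitation materials sent to the intervention arm, so that access to it does not depend on being sampled for measurement. The protocol does not say whether the invitation already carries such a number, so this should be checked.
3. Replace the exclusion rule in Treatment allocation: anyone who has already opted in stays in the randomised arm for Intention-to-treat 1, in line with Statistical analysis and Primary outcome. Report how many opted in.

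The cost is one line of print, one amended sentence and the loss of a few late opt-ins. Forms already sent cannot be recalled, so for those waves the altered exposure of the surveyed half can only be reported.

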### Sample procedures

#### Inclusion criteria for patients

Participants should be at least 18 years old and insured of the KKH statutory health insurance. Moreover, included patients will need to have one or more diagnoses of the following: diabetes, coronary artery disease, asthma, hypertension, heart failure, chronic obstructive pulmonary disease (COPD), chronic depression or schizophrenia. Additional inclusion criteria will be used for each target disease. For example, for patients with type 2 diabetes, hypertension or coronary artery diseases, a risk score for hospital readmission will be calculated. Based on various variables from routine data a logistic regression model was designed to predict hospital readmission using SPSS 19. Those variables are, for example, healthcare costs, international classification of diseases (ICD)-diagnoses, age and gender. This model has been validated by analyzing the receiver operating characteristic curve (ROC) [26] and the positive predictive value [27] and showed valid predictions. If the calculated risk for hospital readmission within the next year is higher than 50%, the person will be included in the study. Patients will be excluded from the study if they have insufficient German language skills, are hard of hearing or are not able to read or use a phone.

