### Outcome assessment

#### Primary outcome

The primary outcome is the time from enrollment until hospital readmission within two years. Time until

hospital readmission will be assessed using routine health insurance data of the KKH that records the date of enrollment in the study as well as the dates of hospital stay.

The routine data will be collected and provided by the statutory health insurance. They are generated during the everyday healthcare business and show the actual healthcare situation of the insurant. Every contact within the healthcare system is represented: doctor and hospital visits with ICD code and Operationen- und Prozedurenschlüssel (OPS) code, the German equivalent to the American procedure coding system (PCS), incapacity to work, the medication and much more. The data are not influenced by non-response or recall-bias as they are assessed directly at the healthcare provider. Routine data depicts accountable variables, but not clinical parameters. The validity of routine data in Germany is not proven, yet studies show that the ICD diagnoses are valid in about 97% for heart failure [29,30]. The routine data are read out by the KKH and securely delivered with pseudonymized codes. The outcomes based on routine data include data of the whole randomized sample of approximately 12,000 insurants.

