### Statistical analysis

Following the intention-to-treat approach we will include all randomized participants in the primary analyses in order to avoid biases such as non-random attrition of participants. As many of the randomized participants decline to take part in the TBHC we run a second intention-to-treat approach, testing the participants versus the control group. Additionally we will perform a sensitivity analysis following the as-treated approach including only participants that have received a minimum of five coaching calls.

Therefore, three different analyses will be performed:

- 1) Intention-to-treat 1: comparing the randomized intervention group (including decliners) versus the control group.
- 2) Intention-to-treat 2: comparing those who took part in the intervention versus the control group (excluding the decliners).
- 3) As-treated: comparing participants who received a minimum of five calls versus the control group.

In order to enhance the comparability of intervention group and control group in the health economic outcomes for analyses 2 and 3, propensity score matching (PSM) will be used to control potential confounding. Routine data from the 12-month period preceding recruitment will be used to match individuals in the intervention group with controls by means of propensity scores. Formally, the propensity score is a person's probability of being assigned to the intervention group given a set of observed covariates. The covariates in the propensity score model will be based on routine data: for example, age, sex, ICD diagnoses, number of days spent in hospital and healthcare costs in the preceding year. The predicted probabilities of unconditional logistic regression models with 'treatment' (intervention versus controls) as dependent variable and the described set of covariates are the basis for the subsequent matching of both groups.

For the primary outcome 'time until hospital readmission' we will use the hazard ratio from a proportional hazard model. Service use and costs will be analyzed by logistic and linear random effects regression models using bootstrapped standard errors.

The secondary outcomes that are patient reported will include different scales, instruments and items with various scale levels. For the analyses of nominal scaled outcomes we will use chi-square tests. Ordinal and interval scaled outcomes will be analyzed using ANOVA

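### Decliners who later opt in to coaching are removed from the trial, which contradicts a primary ITT-1 analysis of everyone randomized

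*Protocol*

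**What the plan says.** Treatment allocation (Protocol) defines the arm: "The randomized intervention group consists of participants and decliners". It adds that decliners get no coaching at first, but "they will have the opportunity to opt in to the TBHC via a telephone number printed on the questionnaires". The consequence of using that number is: "In that case, they will be excluded from the study". No comparable exit is described for controls.

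Statistical analysis (Protocol) sets the primary analysis population: "Following the intention-to-treat approach we will include all randomized participants in the primary analyses". It defines ITT-1 as "comparing the randomized intervention group (including decliners) versus the control group".

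Primary outcome (Protocol) says of the data source: "The outcomes based on routine data include data of the whole randomized sample of approximately 12,000 insurants".

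**The concern.** An opt-in decliner is a randomized member of the intervention arm. Treatment allocation takes that person out; the other two sections keep that person in. Whoever builds the primary data set must break one of the rules, and the protocol does not say which.

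If the exclusion is followed, it has two bad properties. It is one-sided, since only the intervention arm can lose people this way. It also depends on something the person does after randomization, which may reflect a change in health. If the number also appears on follow-up questionnaires, which the protocol neither says nor rules out, a decliner could opt in after a readmission, and exclusion would then depend on the outcome itself.

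ITT-1 is the only one of the three planned comparisons that randomization protects. The Discussion concedes selection bias for ITT-2 and the as-treated analysis but not for ITT-1. ITT-1 is also heavily diluted by the expected 65% of decliners, so a small spurious shift can be large relative to the effect being sought.

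**Working it through.** **1. The flow, checked against the protocol's own figure.** Inputs from Study procedures, Treatment allocation and Power calculation: 12,000 randomized, 5:1 allocation, about 65% declining, half of the decliners mailed.

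- Intervention arm: 12,000 × 5/6 = 10,000. Control: 2,000.
- Decliners: 0.65 × 10,000 = 6,500. Participants: 3,500.
- Decliners mailed: 6,500 / 2 = 3,250.
- Invited to the survey: 3,500 + 3,250 + 2,000 = 8,750. The protocol says approximately 9,000; the difference is 2.8%, so the flow reproduces.

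The opt-in number is printed on the questionnaires, so about 3,250 decliners would see it.

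**2. Share of the arm removed.** Let the opt-in rate among mailed decliners be q (assumed; not in the protocol). The share removed is f = q × 3,250 / 10,000.

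- q = 1%: about 33 people, f = 0.3%
- q = 5%: about 163 people, f = 1.6%
- q = 10%: 325 people, f = 3.25%, or about 3.3%

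No controls are removed. Losing 5% of the arm (500 people) would need 500 / 3,250 = 15% of mailed decliners to opt in; losing 10% (1,000 people) would need 31%.

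**3. Shift in the hazard ratio with no true effect.** Let g be the readmission hazard of those removed relative to those kept (assumed 0.5 to 2, because the direction is unknown). The control arm keeps its equivalents of those removed, so approximately HR = 1 / (1 − f + f·g).

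- q = 1%: 0.997 (g = 2) to 1.002 (g = 0.5)
- q = 5%: 1 / 1.01625 = 0.984 to 1 / 0.991875 = 1.008
- q = 10%: 1 / 1.0325 = 0.969 to 1 / 0.98375 = 1.017

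**4. Effect on the type I error.** The standard error of the log hazard ratio is 1 / √(D × 5/36), with D events. Assuming 50% to 75% of the 12,000 have an event, D = 6,000 to 9,000 and the standard error is 0.035 to 0.028. For a two-sided nominal 5% test:

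- q = 1%: 5.0% to 5.2%
- q = 5%: 7.5% to 8.8% at g = 2; 5.6% to 6.0% at g = 0.5
- q = 10%: 15% to 20% at g = 2; 7.6% to 8.9% at g = 0.5

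**5. Sensitivity to the approximation.** The formula in step 3 ignores that high-risk people leave the risk set early. A Cox fit to exponential times, with an assumed 50% one-year risk and censoring at 24 months, gives for q = 10% a hazard ratio of 0.980 at g = 2 and 1.022 at g = 0.5. With 9,000 events the type I error is then about 11% and 12%. The range of roughly 0.97 to 1.02 covers both calculations.

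**6. Scale.** With D = 6,000 to 9,000, the hazard ratio detectable with 80% power is exp(−2.80 × standard error) = 0.91 to 0.92. For dilution, suppose coaching gives participants a hazard ratio of 0.90 and that participants and decliners have equal baseline risk (both assumed). ITT-1 would then show about 0.35 × 0.90 + 0.65 = 0.965. A spurious 0.984 is ln 0.984 / ln 0.965 = 0.45 of that on the log scale.

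**The case against.** The strongest reply is that the protocol commits to full intention-to-treat several times and departs from it in one sentence. Power calculation, Primary outcome and Statistical analysis all refer to the total or whole randomized sample. The opt-in number is printed on the questionnaires, so the exclusion may be meant only for the questionnaire part. Study procedures also uses inclusion in the study narrowly: invitees enter as participants only once they return the confirmation, yet decliners are still analysed in ITT-1. This stands in part. It rules out the flat statement that the primary analysis is not intention-to-treat; what the text shows is an unresolved contradiction. It does not remove the contradiction, because the sentence sits in the trial-wide allocation section and carries no limit to the survey.

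A second objection is that the bias may be trivial. At 1% opt-in it is, and nothing in the protocol shows whether those who opt in are sicker or healthier.

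A reader might go further and infer that the exclusions for language, hearing, reading and phone use ("Patients will be excluded from the study if they have insufficient German language skills, are hard of hearing") also operate in the intervention arm only, because only that arm gets an acquisition call. The protocol does not support this. It gives no method or time for assessing these criteria. Study procedures has eligibility settled before randomization, classes invitees who do not return the confirmation as decliners (kept in ITT-1), and mails questionnaires to controls as well. Nowhere does it say that anyone is dropped at the call. Differential detection is a fair question, not a stated defect.

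**Conclusion.** The concern holds as a contradiction between Treatment allocation on one side and Primary outcome and Statistical analysis on the other. If the exclusion is applied to the routine-data outcome, ITT-1 loses people from one arm because of what they did after randomization and is no longer intention-to-treat.

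Under the assumptions above, the likely size is small to moderate and its direction is unknown. It is negligible at the low end of the opt-in range; at 10%, the type I error could roughly double or more, reaching 15% to 20% in the least favourable case. The opt-in rate, the relative hazard and the event proportion are all assumptions. Larger distortions need implausibly many decliners to change their minds. The case for acting rests on the contradiction and the cheap remedy, not on a demonstrated large bias.

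**What to change.** In Treatment allocation, replace the exclusion sentence with wording such as: Decliners who opt in to coaching remain in the study and are analysed in their randomized intervention arm in ITT-1 for all routine-data outcomes; any exclusion applies at most to the separate decliner group in the questionnaire analyses.

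At most, add one clause saying that anyone found after randomization to meet a language, hearing, reading or phone criterion also stays in ITT-1. The eligibility criteria need no rewriting.

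The cost is a sentence or two. The insurer's routine data are said to cover the whole randomized sample already, so no new collection is needed. Some decliners in ITT-1 will have been coached late, which is consistent with analysing people as randomized.
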